**COLLABORATING INSTITUTIONS**

**University of California San Francisco:** UCSF is the only University of California campus dedicated exclusively to the health sciences and is home to graduate professionals in medicine, nursing, pharmacy, and dentistry, and a graduate division for pre-doctoral and postdoctoral scientists. In addition to its main campus, where the Schools of Medicine, Nursing, Pharmacy, and Dentistry and the UCSF Medical Center are located, UCSF encompasses several major sites in San Francisco, including UCSF Mount Zion, the Comprehensive Cancer Center, and Mission Bay. UCSF is considered one of the nation's premier health sciences, training, and research centers and has a well-established reputation in biomedical research.

**Kenya Medical Research Institute (KEMRI):** The Kenya Medical Research Institute (KEMRI) is one of the leading health research institutes in Africa. KEMRI was established in 1979 under the Science and Technology (Amendment) Act of that year to represent the national body responsible for carrying out health science research in Kenya. KEMRI's mission is to conduct health research and generate research findings to be applied towards improvement of health in Kenya and the world over. Under the Amendment Act, the KEMRI was charged with the responsibility of carrying out health research with the following mandates:

- To carry out research in the field of biomedical sciences;
- To co-operate with other organizations and other institutions of higher learning in training programs and on matters of relevant research;
- To liaise with other research bodies within and outside Kenya carrying out similar research;
- To disseminate research findings;
- To co-operate with the Ministry of Health, the Ministry responsible for research, the National Council for Science and Technology, and the Medical Science Advisory Committee on matters pertaining to research policies and priorities.

With health research and training expertise in infectious disease, parasitic disease, epidemiology, and biotechnology and non-communicable diseases, KEMRI has grown to become one of the leading centers of excellence in health research development and Africa's largest health research institute. KEMRI has trained cadres of professionals and maintains over 80 professors with PhD degrees or equivalent, over 148 with MA or equivalent, and nearly 400 highly trained and skilled technical staff. As a partner in global health initiatives, KEMRI collaborates with the World Health Organization (WHO), the Japan International Cooperation Agency (JICA), U.S. Center for Disease Control and Prevention (CDC), among others. KEMRI serves as the Collaborating Center for HIV/AIDS, Tropical Research, Polio Immunization, Viral Hemorrhagic Fevers, and Anti-Microbial Resistance.

**Bixby Center for Global Reproductive Health, UCSF:** The UCSF Bixby Center for Global Reproductive Health was formed in 1999 to address the health, social, and economic consequences of sex and reproduction through research and training in contraception, family planning, and STIs. The Bixby Center strives to develop preventive solutions to the most pressing domestic and international reproductive health problems. The Bixby Center is currently carrying out over 100 domestic and international projects in the areas of abortion and post-abortion care, adolescent sexuality and reproductive health, contraceptive development and family planning, HIV/AIDS and other STIs, safe motherhood, and unintended pregnancy.

**Ibis Reproductive Health:** Ibis Reproductive Health is a non-governmental organization that aims to improve women's reproductive autonomy, choices, and health worldwide by conducting original clinical and social science research, leveraging existing research, producing educational resources, and promoting policies and practices that support sexual and reproductive rights and health. The organization was founded in 2002 to support talented new clinical and social science researchers committed to studying critical, yet often overlooked, topics in the reproductive health field. With the promotion of women's sexual and reproductive autonomy as the guiding principle of its work, Ibis's staff tackles the full spectrum of cutting-edge reproductive health and rights topics in the U.S., Sub-Saharan Africa, Latin America, and the Middle East and North Africa. Ibis's staff of roughly twenty is located in offices in Cambridge, Massachusetts (headquarters); Johannesburg, South Africa; and San Francisco, California.

## **ABSTRACT**

Approximately three quarters of the world's population living with HIV/AIDS live in Sub-Saharan Africa, and 60 percent are estimated to be women. Globally, fourteen million children have lost one or both parents to HIV/AIDS, and it is estimated that 80% of these children orphaned from HIV/AIDS live in Sub-Saharan Africa[1]. Additionally, more than 90% of all pediatric HIV infections are due to maternal-child transmission of HIV, and more than 90% of these pediatric infections are in Sub-Saharan Africa[2]. Increased use of family planning among HIV-infected individuals would help to decrease the number of unintended pregnancies among HIV-infected women thereby decreasing both the number of children who are orphaned from HIV/AIDS and the number of children who are infected with HIV. Additionally, decreasing unintended pregnancies among HIV-infected women in Sub-Saharan Africa is expected to decrease maternal mortality. Maternal mortality in several Sub-Saharan African countries has increased as HIV prevalence among reproductive age women has risen[3].

In 2003 the President's Emergency Plan for AIDS Relief (PEPFAR) initiative was created to increase HIV prevention and treatment programs in 15 countries in Africa. Since 2004 there has been a rapid scale-up in treatment programs in all PEPFAR-funded African nations. Unfortunately family planning services has not been included in this initiative, leaving HIV-infected women to seek family planning services elsewhere. Several national and international conferences have been held focusing on the integration of family planning services into HIV care and treatment. The consensus among multiple local and international public health organizations and funding agencies is that integration of family planning and HIV care in Sub-Saharan African countries is of utmost importance in order to decrease the rate of HIV infection transmission and the societal impact of HIV infection[4-9]. Despite the recent international attention to the idea of integrating family planning into HIV care and treatment, few studies have evaluated the most effective models of integration and their outcomes. We propose conducting a cluster randomized trial comparing the integration of family planning services into HIV care and treatment programs versus the standard referral for family planning services outside of HIV care and treatment programs within Suba, Kisumu East, Rongo and Migori districts in Nyanza province;

The objectives of this research are:

1. To assess the impact of integrating family planning services into HIV care and treatment on the utilization of family planning by HIV-infected women and men.
2. To estimate the impact of integrating family planning services into HIV care and treatment on unintended pregnancies among HIV-infected woman; and
3. To assess the feasibility and acceptability of integration of family planning into HIV care and treatment programs.

We hypothesize that the integration of family planning services into HIV care and treatment will increase the utilization of more effective contraception (MEC) (including oral, implantable, injectable, and intra-uterine methods) among HIV-infected women. We hypothesize that by increasing the utilization of MEC, contraceptive compliance and continuation among HIV-infected women will increase and unintended pregnancy rates among HIV-infected women will decrease. This study will help us understand the acceptability and feasibility of integrating family planning services into HIV care and treatment programs. It will also help describe the effects of integration on contraceptive use, unintended pregnancies, and HIV care.

## **BACKGROUND AND JUSTIFICATION**

### **There is a need for increased family planning services for people living with HIV infection in Sub-Saharan Africa.**

Recent studies suggest a large unmet need for contraception among HIV-infected women in Africa receiving antiretroviral therapy (ARV)[9]. Family planning services, however, remain separate from HIV care and treatment services, leaving many HIV-infected women without resources for preventing pregnancy. The integration of family planning services into HIV care and treatment programs would have multiple public health benefits by preventing adverse consequences of pregnancy for HIV-infected women and by providing women with the opportunity to make reproductive choices.

The paradigm of integrating family planning into HIV services is being promoted by multiple international public health agencies and foundations, as well as local organizations. This public health initiative could result in fewer unintended pregnancies, and therefore decrease mother-to-child HIV transmission, illegal abortion, maternal and neonatal morbidity and mortality, and various other health and societal cost outcomes related to unintended pregnancies and vertical transmission of HIV[4, 5]. Despite this new interest in the integration of family planning into HIV services, very few studies have evaluated the clinical impacts of integration. By decreasing the pregnancy rate in HIV-infected women, family planning services are expected to decrease maternal mortality rates in Sub-Saharan Africa, which have risen alongside increases in HIV prevalence[3]. Similarly, by decreasing the pregnancy rate in HIV-infected women, family planning services would help to decrease neonatal morbidity and mortality, such as stillbirth, low birth weight, and prematurity, all of which are common among infants of HIV-infected women[10].

As in much of Sub-Saharan Africa, actual fertility among women in Kenya is significantly higher than wanted fertility[11]. In Kenya and Zambia, over 50 percent of births over a five and three-year period, respectively, were found to be unintended, many to women with unknown HIV status[12, 13]. In Uganda 97 percent of pregnant, HIV-infected women who had been offered antiretroviral treatment (ART) in rural Uganda did not want to be pregnant[9]. Despite the high rates of unintended pregnancy, contraceptive prevalence in sub-Saharan Africa is low, with only 13% of married, reproductive-aged women using contraception in 2002[14].

People living with HIV/AIDS, policy makers, and service providers feel that integration of family planning into HIV care is the logical solution to meet the unmet need for family planning services. In Uganda, a group of people living with HIV/AIDS desired increased access to contraception and preferred to receive family planning services where they receive HIV care. They reported preferring providers who already knew them and not having time to access other services at a different location[15]. Women reported feeling that integrated services would help them change their partners' negative views on family planning since they could attend sessions together[16]. In Kenya, the majority of HIV care providers interviewed in a study reported a high unmet need for family planning among HIV-infected individuals because of reluctance to visit family planning clinics due to negative attitudes among providers toward people with HIV[6]. Policy makers and providers in Kenya view the rational next step to be integration of family planning into HIV services, believing that the integration of the two could complement each other, reduce cost and time for clients and services, and improve client follow-up[6]. Taken together, these studies suggest that HIV-infected patients, HIV-care providers and local policy makers all see a need to expand family planning services for HIV-infected individuals in Sub-Saharan Africa.

This proposed study will be conducted in the Suba, Kisumu East, Rongo and Migori districts of the Nyanza Province of Kenya. It will be conducted within the Family AIDS Care and Education Services (FACES), which is funded primarily through the US President's Emergency

Plan for AIDS Relief (PEPFAR) via the Center for Disease Control (CDC). FACES began services in March 2005 in Nyanza Province and is a collaboration between the Kenya Medical Research Institute (KEMRI) and the University of California, San Francisco (UCSF). FACES' mission is to provide accessible comprehensive care and support services to HIV affected families and other vulnerable populations, reinforce prevention practices, and build capacity related to HIV/AIDS care. FACES partners with government health facilities to provide HIV care, treatment, and support to individuals and families in the Nyanza province and currently has over 13,000 patients enrolled in care and over 3,000 on antiretroviral therapy (ART). The Nyanza province has the highest HIV prevalence in Kenya, with 18.3% of women and 11.6% of men aged 15-49 estimated to be infected in 2003[15]. FACES data suggests that contraception prevalence ranges somewhere between 23-35 percent[17]. Because family planning services are not currently provided in an integrated manner within the care facilities that FACES currently works in or those where it will expand to within the 2007-2009 fiscal years in Suba, Kisumu East, Rongo and Migori Districts, this setting affords an excellent opportunity to study the effect of integration on critical indicators of contraceptive use.

### **There are data to support the hypothesis that integration of family planning into HIV care would be effective.**

Several studies have shown that integrating family planning services into HIV voluntary counseling and testing increases contraceptive use and decreases unwanted pregnancies[18-20]. Additionally, a few theoretical and/or cost-effectiveness studies have estimated that provision of family planning to HIV-infected women via integration of family planning into HIV care programs would decrease unintended pregnancies and maternal-child HIV transmission rates, and would be cost-effective. One study demonstrated that moderate reductions in unintended pregnancies rates of HIV-infected women (estimates varied by country) would result in the equivalent number of HIV-infected births averted as would current prevent mother-to-child transmission (PMTCT) efforts using Nevirapine [21]. Another model demonstrated that integration of family planning into PMTCT services could avert approximately two times the number of child HIV infections (71,000 versus 39,000) that current PMTCT services are estimated to prevent[22]. A cost-effectiveness analysis concluded that providing family planning and increasing contraception use among HIV-infected women who do not want to be pregnant is as cost-effective as current PMTCT programs providing Nevirapine and averts almost 30 percent more HIV-positive births than does PMTCT programs with Nevirapine [23]. Thus, there is experience with combining family planning with voluntary counseling and testing services, and there are projected data to show that integration of family planning and HIV care services would succeed at decreasing both unintended pregnancies and HIV transmission, and would be cost-effective.

### **Preliminary data**

In 2006, we performed an internal service provision improvement evaluation of the reproductive health services at FACES clinics[24]. The evaluation consisted of 24 structured observations of all types of client interactions, including Voluntary Counseling and Testing (VCT), HIV (peer) education, adherence counseling, enrollment visits, clinical and non-clinical follow-up visits, and family counseling sessions.

Several barriers to effective reproductive healthcare were identified: environmental barriers (related to space, examining equipment, contraceptive methods available, cultural discomfort, technical discomfort with gynecologic exams); lack of inclusion of reproductive health history into enrollment and follow-up visits; lack of inclusion of family planning counseling/care into routine clinic visits; long intervals between client request for family planning and actual method initiation; and lack of family planning counseling training/experience among clinic staff.

The evaluation revealed that only 20% of the observed clinical encounters involved any family planning (FP) counseling and only 16% of clinical encounters involved spontaneous, provider-initiated FP information. The content of the FP counseling varied greatly. Despite a space on the intake form for the date of the last menstrual period, frequently when answers of greater than one month were given, an evaluation for pregnancy was not performed. This inadequate response to delayed menses raises the concern of the occurrence of unintended pregnancies, potential teratogenicity of HIV medication when pregnancy is not detected, and missed opportunities for early referral to antenatal care. Additionally, despite prompts on the clinical intake forms, providers were observed to inquire about sexual activity and contraception use only approximately 30% of the time. Only three of the observed clinical encounters resulted in steps towards contraception initiation and only one of the 24 observed clinical encounters involved any discussion of screening for risks involved with different contraceptive methods.

This assessment of reproductive health services at FACES is limited by a small sample size and non-standardized method of observation and evaluation. However, certain themes do emerge having to do with inadequate counseling and assessment of patient's reproductive needs/desires, insufficient technical support with offering reproductive health services, inadequate training in family planning counseling for clinicians, and scarce method supply and ability to initiate contraception at time of discussion of patient's need/desire to contracept. These findings blatantly illustrate the need for improvement of family planning and other reproductive health services within the FACES HIV care and treatment programs. It is also likely that these qualitative findings from the FACES centers would be similar at other HIV care and treatment programs throughout Kenya and Sub-Saharan Africa.

## **HYPOTHESIS**

We hypothesize that the integration of family planning services into HIV care and treatment will increase the utilization of all modern contraceptive methods, especially more effective contraception (MEC) (including oral, implantable, injectable, and intra-uterine methods), among HIV-infected women. Additionally, we hypothesize that by increasing the contraceptive prevalence, contraceptive compliance and continuation among HIV-infected women will increase and unintended pregnancy rates among HIV-infected women will decrease.

## **GENERAL OBJECTIVES**

The general objective of this study is to determine whether an integrated model of family planning provision at HIV care and treatment centers better addresses the family planning needs of HIV-infected people and their partners than the existing non-integrated model. The results of the study will provide information for policy makers and program planners that will help them implement high quality family planning services for this population.

## **SPECIFIC OBJECTIVES**

1. To compare the contraceptive prevalence among HIV-infected individuals receiving care at PSCs randomized to the integrated model to that of HIV-infected individuals at control (non-integrated) PSCs
2. To compare the proportion of pregnancies that are unintended among HIV-infected women receiving care at PSCs randomized to the integrated model to that of HIV-infected women at control (non-integrated) PSCs

3. To assess the feasibility and acceptability of integration of family planning into HIV care and treatment programs;
4. To evaluate knowledge of contraception and the importance of dual method use among HIV-infected women;
5. To better understand the pregnancy intentions of HIV-infected women and men who seek health care services in Migori, Rongo, Kisumu East and Suba Districts

## **STUDY DESIGN/METHODOLOGY**

### **Overview**

The study will have three parts. During the first part (3 months), baseline data on contraceptive prevalence and unintended pregnancy will be collected at 18 PSCs that are supported by the FACES program in Suba, Kisumu East, Rongo and Migori Districts. Also during this first part, information about knowledge, attitudes and practices related to family planning will be obtained from patients and from clinicians at the sites. During the second part (3 months), an intervention consisting of integrating family planning services will be designed and implemented at twelve of the 18 FACES-supported PSCs. We aim to utilize a 2:1 integration:control model, with delayed integration so as to gradually expand the integration of FP and HIV services throughout the 18 sites, while maintaining the ability to test hypotheses on the effects of integration on health outcomes. After collecting the baseline data, we plan to stratify the clinics into two categories based on the overall patient volume and differences in the structure of family planning provision, i.e., whether or not there is a specific MCH division providing family planning at the site or not. Randomization of sites will then occur among clinics in each of these strata, with a ratio of two intervention sites (integrated model) to one control site (family planning provided in the standard manner at the site). During the third and last part (9 months), data on contraceptive prevalence and unintended pregnancy will be collected from each of the 18 sites. At the end of part three, information about knowledge, attitudes and practices related to family planning again will be obtained from female patients and from clinicians at the sites. In addition, we will administer questionnaires assessing the acceptability of family planning services to patients, and in addition clinic staff will be answer a questionnaire assessing the feasibility of providing integrated family planning services.

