## 2.2 Intervention implementation

After the intervention is fully designed, it will be implemented at twelve “intervention” FACES-supported PSC’s using a model that will ultimately include integrating HIV and FP services in all 18 sites. Implementing the intervention will consist of:

- Training clinic staff in family planning counseling and method provision
- Introducing family planning assessments into all clinic visits via incorporating inquiries as to family planning needs on all medical forms, thereby prompting provider questioning
- Introducing new client counseling sessions and education materials into the PSC care infrastructure
- Devising a system of procuring, inventorying and dispensing contraceptive methods, including at the very least condoms, oral contraceptives and injectables. At sites where it is feasible, IUDs and implants will also be made available. When a method is not available at the site (such as in the case of surgical sterilization), clients will be referred to nearby centers that offer the method.

At both the intervention and control sites, a brief family planning module will be integrated into the standardized clinic encounter form that is used at each client visit. This module will prompt the clinician to ask if the client is currently using contraception and his or her fertility intentions. Simply put, if the client is using a method, the provider will be ask if he or she is interested in changing the method; if the client is not using a method and does not desire pregnancy, the provider will be ask if he or she is interested in starting a method.

- At “intervention” sites clients will then be extensively counseled about contraception and will be provided any needed contraceptive methods on site.
- At “control” sites, clients will be provided with contraceptive services through the centers’ standard mechanisms, which generally involve referral to an affiliated family planning program that may or may not be on-site.

Prior to implementation of our intervention, we will resubmit the protocol for review at SSC/ERC for review of the final design of any educational materials developed.

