## **TIME FRAME**

### **Study Timeline:**

|                                                                                           | Dec-
'07-
Jan '09 | Feb-
Mar '09 | Apr-
May
'09 | Jun-Jul
'09 | Aug-
Sep '09 | Oct-
Nov
'09 |
|-------------------------------------------------------------------------------------------|-------------------------|-----------------|--------------------|----------------|-----------------|--------------------|
| Conduct baseline site-based data collection                                               | X                       | X               |                    |                |                 |                    |
| Conduct baseline acceptability questionnaires and interviews with female and male clients | X                       | X               |                    |                |                 |                    |
| Finalize design of family planning integration model                                      | X                       | X               |                    |                |                 |                    |
| Conduct baseline interviews with                                                          | X                       |                 |                    |                |                 |                    |

|                                                                                            |  |   |   |   |   |   |
|--------------------------------------------------------------------------------------------|--|---|---|---|---|---|
| providers on knowledge, attitudes and practices related to family planning                 |  |   |   |   |   |   |
| Train clinicians and community health workers in integrated model                          |  | X | X |   |   |   |
| Implement the intervention at all sites                                                    |  | X | X |   |   |   |
| Post-integration data collection at all sites on pregnancy status and contraceptive use    |  |   | X | X | X | X |
| Conduct follow-up acceptability questionnaires and interviews with female and male clients |  |   |   | X | X |   |
| Interviews with providers on acceptability and feasibility                                 |  |   |   | X | X |   |
| Data analysis                                                                              |  |   |   |   |   | X |

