## **EXPECTED APPLICATION OF RESULTS**

If integration of family planning services into HIV care and treatment appears feasible, acceptable, and effective at decreasing unintended pregnancies among HIV-infected women, the family planning intervention will be introduced into all FACES-supported PSC clinics. If the intervention does not appear to be feasible, acceptable, or effective based on the results of the trial, assessment of the integration will be conducted to try to identify ways in which the family planning intervention could be improved or changed. Modification of the intervention and reintroduction of it into HIV care and treatment will be considered based on trial results.

Ultimately, the findings of this research will help guide future research, policy, and interventions in the area of integrating family planning into HIV care. The ultimate goal is to create a feasible, acceptable, and effective family planning intervention that can be modified and applied elsewhere in Kenya and throughout Sub-Saharan Africa in order to increase access to effective contraception among HIV-infected women, thereby allowing them to make reproductive choices and to decrease unintended pregnancies.

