### **KEMRI**

#### Personnel (all staff receive benefits at 15%)

- [name] will serve as Site PI and will be supported at 1% effort. [name] will give additional in-kind support of approximately 9%.
- A nurse/researcher will serve as the Family Planning coordinator to coordinate the project and will be supported full-time.
- An assistant coordinator also trained as a nurse will also be supported full-time.
- Four nurses who specialize in family planning will be supported full-time to mentor and assist clinicians with FP integration at the 18 sites.
- Three interviewers will be hired to conduct interviews with clients and clinicians.
- Three data clerks will be supported full-time to perform data entry for the electronic medical records (OpenMRS system) and manage the data. An additional \$3,000 is requested to support approximately 80% of an additional data clerk to perform data entry for the surveys and questionnaires detailed in the proposal.
- [name], the FACES Program Manager based at KEMRI, will be supported at 10% to perform administrative duties and supervise financial management.
- [name], a statistician based at KEMRI, will be supported at 5% to assist with data analysis.
- Health insurance costs of \$3,934 are requested to provide the twelve 100% EFT employees with health insurance. The current health insurance premium is 20,000 Ksh per annum per 100% EFT employee; this translates into \$327.87 US dollars.

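### The protocol contradicts itself on whether the six control sites are integrated only after favourable results, and nowhere says they stay non-integrated until the month-15 data are complete

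*Protocol*

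**What the plan says.** **Extension without a condition or date.** The Overview under Study Design/Methodology describes 2:1 allocation "with delayed integration so as to gradually expand the integration of FP and HIV services throughout the 18 sites". The same sentence goes on to say that the ability to test the hypotheses is to be kept. Section 2.2 describes implementation at twelve sites "using a model that will ultimately include integrating HIV and FP services in all 18 sites".

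**Extension with a condition.** Expected Application of Results begins "If integration of family planning services into HIV care and treatment appears feasible, acceptable, and effective at decreasing unintended pregnancies among HIV-infected women", and only then says "the family planning intervention will be introduced into all FACES-supported PSC clinics". For an unfavourable result it says "Modification of the intervention and reintroduction of it into HIV care and treatment will be considered based on trial results".

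**Activity at all sites.** The Study Timeline has a row "Implement the intervention at all sites", marked for February-March and April-May 2009. Post-integration data collection is marked from April-May to October-November 2009. The KEMRI personnel justification says that four family planning nurses "will be supported full-time to mentor and assist clinicians with FP integration at the 18 sites". The stated budget period is 1 November 2008 to 31 October 2009.

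**The comparison.** Section 3.1 collects outcomes over months 7-15 at twelve intervention and six control sites. Endpoints compares the arms over the same period. Section 2.2 gives control clients services through each site's standard mechanisms. The Data analysis plan classifies facilities as randomized.

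**The concern.** There are two problems.

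The first is a contradiction on conditionality. If the result is unfavourable, the Overview and section 2.2 still bring integration to all six control sites, while Expected Application of Results withholds general introduction and only considers a modified version. The 18 study sites are FACES-supported, so the conditional rule covers the controls. Both statements cannot hold.

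The second is timing. The primary comparison needs six non-integrated sites through months 7-15. Staff who followed the timeline row and the nurse allocation as written would bring integration or mentoring into control sites during follow-up and could cite the protocol for doing so. Because analysis follows allocation, that time would count as control time and narrow the measured difference. Contrast lost in this way cannot be recovered afterwards.

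**Working it through.** **Step 1: the sections side by side**

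| Section | Sites integrated or supported | Condition | Timing |
|---|---|---|---|
| Overview | 18, gradually | none | delayed, no date |
| 2.2 | 12, ultimately 18 | none | no date |
| Expected Application of Results | all FACES-supported clinics | favourable results | after results |
| Study Timeline | all sites | none | Feb-May 2009 |
| KEMRI personnel | 18 | none | within budget year to 31 Oct 2009 |
| 3.1, Endpoints | 12 intervention, 6 control | – | months 7-15 |

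The timeline's implementation row overlaps data collection in April-May 2009. The budget year covers April to October 2009, seven of the eight calendar months (April to November) marked for collection.

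**Step 2: reproduce the planned power**

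Inputs from Sample size considerations: 22% against 30%, two-sided alpha 0.05, ICC 0.01, about 140 women per site, 12 and 6 sites.

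- Design effect = 1 + (140 − 1) × 0.01 = 2.39.
- Effective numbers: control 840/2.39 = 351; intervention 1,680/2.39 = 703.
- Power is 79.3% (z-test, pooled variance) or 81.4% (z-test, unpooled), which agrees with the stated 80%.
- For a t-test on 18 − 2 = 16 degrees of freedom, SE = √(0.22 × 0.78 × 2.39/840 + 0.30 × 0.70 × 2.39/1,680) = 0.0281. The non-centrality is 0.08/0.0281 = 2.85, the critical value is 2.12, and power is 76%.

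**Step 3: illustrate dilution**

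Assumption, not in the documents: a share f of control follow-up is integrated and takes the full effect at once. Control prevalence is then 0.22 + f × 0.08. With f = 0.10:

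- control prevalence = 0.228, difference = 0.072;
- SE = √(0.228 × 0.772 × 2.39/840 + 0.30 × 0.70 × 2.39/1,680) = 0.0283;
- non-centrality = 0.072/0.0283 = 2.55, and power is 67% (t, 16 df).

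The z-test shows the same pattern: one integrated month of nine at all control sites (difference 7.1 points) lowers pooled-z power from 79% to 69%.

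**The case against.** The strongest reply is that the intent is clear. The sentence in the Overview ties the delay to keeping the hypothesis test. Specific Objectives calls the controls non-integrated, section 2.2 and the potential-benefits section give their clients standard services, and section 3.1 and Endpoints hold the 12:6 comparison over the same nine months. On this reading, delayed and ultimate integration means after data collection. The conditional text concerns policy once results exist and cannot affect data already collected. The nurse count sits in a budget justification whose figures do not track the design closely: it funds 640 client interviews, while the end-of-study survey alone plans 976. Project work at all 18 sites is also expected, since the family planning module goes onto encounter forms in both arms.

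Most of this stands. A reader might infer that control sites cross over during months 7-15, or that gradual expansion means a stepped roll-out exposing a large share of control time. The documents support neither: no section schedules control integration in that window, and any exposure share is assumed.

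The reply does not remove two things. Intent fixes no date, and the timeline row and nurse allocation are what staff would work from. The disagreement on conditionality also remains wherever the date falls.

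**Conclusion.** The protocol is inconsistent in two respects: whether control-site integration depends on results, and how many sites receive integration activity while outcomes are collected. The controls are meant to stay non-integrated, but no sentence says they do so until the month-15 data are complete. This is more than missing detail, because carrying out the timeline and the nurse allocation as written would put integration support into control sites during follow-up.

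The size of any dilution is unknown. The fall from about 76% to 67% at 10% integrated control time is an illustration that rests on the protocol's own inputs, a t-test on 16 df and an assumed full immediate effect. It is not a forecast. If no control site is integrated before month-15 collection ends, the planned 8-point contrast is untouched.

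**What to change.** Reconcile the Overview, section 2.2, the Study Timeline, Expected Application of Results and the KEMRI personnel justification.

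1. State once whether integration at the six control sites is conditional on the trial's results. Which rule applies is for the sponsor to settle.
2. To protect the concurrent comparison the protocol already describes, state that neither integration nor integration mentoring starts at a control site until month-15 data collection is complete.
3. Make the timeline row and the nurse allocation refer to the twelve intervention sites for that period, and describe separately any other nurse work at control sites.
4. If a control site is nevertheless integrated early, keep the analysis by allocated arm as primary and record the date for a sensitivity analysis. Truncating all sites at the first such date is not advised, since it could discard late data from all 18.

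The cost is wording in five places and one recorded date. The downside is that control sites wait until the end of data collection.
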